## Abstract

**Background:**

Falls are one of the most common health problems among older people and pose a major economic burden on health care systems. Exercise is an accepted stand-alone fall prevention strategy particularly if it is balance training or regular participation in Tai chi. Dance shares the ‘holistic’ approach of practices such as Tai chi. It is a complex sensorimotor rhythmic activity integrating multiple physical, cognitive and social elements. Small-scale randomised controlled trials have indicated that diverse dance styles can improve measures of balance and mobility in older people, but none of these studies has examined the effect of dance on falls or cognition. This study aims to determine whether participation in social dancing: i) reduces the number of falls; and ii) improves cognitive functions associated with fall risk in older people.

**Methods/design:**

A single-blind, cluster randomised controlled trial of 12 months duration will be conducted. Approximately 450 participants will be recruited from 24 self-care retirement villages that house at least 60 residents each in Sydney, Australia. Village residents without cognitive impairment and obtain medical clearance will be eligible. After comprehensive baseline measurements including physiological and cognitive tests and self-completed questionnaires, villages will be randomised to intervention sites (ballroom or folk dance) or to a wait-listed control using a computer randomisation method that minimises imbalances between villages based on two baseline fall risk measures. Main outcome measures are falls, prospectively measured, and the Trail Making cognitive function test. Cost-effectiveness and cost-utility analyses will be performed.

**Discussion:**

This study offers a novel approach to balance training for older people. As a community-based approach to fall prevention, dance offers older people an opportunity for greater social engagement, thereby making a major contribution to healthy ageing. Providing diversity in exercise programs targeting seniors recognises the heterogeneity of multicultural populations and may further increase the number of taking part in exercise.

**Trial registration:**

Australian New Zealand Clinical Trials Registry ACTRN12612000889853

The trial is now in progress with 12 villages already have been randomised.

## Background

Public health systems across the world are facing the challenge of greater longevity and consequently increasing numbers of age-related adverse health conditions. Falls are among the most common age-related health problems for older adults in developed countries [1], including Australia [2]. For example, in New South Wales, the most populous Australian state, one in four adults aged 65 years and older fall annually, and 10% of these falls result in hospitalisation [3]. The consequences of a fall even without physical injury are grave: falls can lead to fear of falling, poor quality of life, loss of independence, and nursing home admission [4,5]. The direct health care cost of fall-related injuries was estimated at AUD$558.5 million, or nearly 5% of the total health care budget of NSW, in 2006/7 and it is expected to triple by 2050 based on demographic shifts alone [6], unless effective preventive strategies are put in place.

Exercise is an accepted stand-alone strategy which addresses the physiological deficits that are part of the multi-factorial aetiology of falls; systematic reviews report that exercise programs reduce fall rates by an average of 16% [7,8]. As a result, exercise interventions now form part of clinical guidelines for fall prevention in the United States (US), United Kingdom (UK) [9] and Australia [10]. Most programs target fitness dimensions (e.g., muscle strength, aerobic capacity, balance, agility) are delivered (a) with a focus on one dimension only, or (b) in combination, but in a segmented ‘stop-start’ manner. These approaches may not be the best ways to optimise benefits. For example, Tai chi interventions have been shown to reduce the risk of falls by 37% compared to 22% in multi-component group-based exercise [8]. Tai chi integrates multiple physical and cognitive elements that are claimed to be synergetic and involve the whole “body-mind system” rather than a composite of separate components [11].

Dance also shares the ‘holistic’ practice approach. It is a complex sensorimotor rhythmic activity integrating multiple physical, cognitive and social elements, all of which have the potential to ameliorate a wide range of physiological and cognitive fall risk factors. Furthermore, unlike exercise programs that require training for specialised instructors, dancing is already available in the community and therefore inherently sustainable.

The potential of dance as a promising alternative to existing fall prevention exercise was first mooted in the public health literature in 2003, albeit with limited empirical support, mostly inferred from studies of exceptional balance abilities of professional young dancers [12]. Since then, an increasing number of dance-based studies involving older adults have been published [13], supporting the benefits of dance in improving impaired gait and balance, two of the strongest risk factors for falls in older people [14]. For example, cross-sectional studies have shown that seniors who dance have superior balance and gait characteristics compared to aged-matched controls [15,16]. Small-scale (≤50 participants) randomised controlled trials (RCTs) have also shown that a variety of dance styles result in improved balance and gait speed of older people [17-21]. Yet, none of the intervention studies, whether RCTs or quasi-experimental [22-25], examined whether these programs also reduced the incidence of falls or addressed cognitive risk factors for falls [5,26-28].

This study aims to determine whether a typical community social dance program i) reduces the number of falls; and ii) improves cognitive factors associated with fall risk in older people. We hypothesise that dance will lead to at least a 37% reduction in the incidence of falls, based on the pooled effect size of Tai chi trials, [8] and that its effect on cognitive function will be at least as strong as that resulting from other aerobic training (e.g., walking on treadmill) interventions [29].

## Methods

### Design

A single-blind, cluster randomised controlled trial, will be conducted in self-care retirement villages (clusters) as described in the study flow chart (Figure 1). Ethics approval has been granted by the Human Research Ethics Committee (ref: 9468) University of Western Sydney and the trial has been registered with the Australian and New Zealand Clinical Trials Register (ACTRN12612000889853).

**Figure 1 F1:**
[figure not shown]
Study flow chart.

### Recruitment

Independent care residents of participating villages will be invited to attend an information session. Residents will be made aware of the information session via their village’s internal mail system and other channels (e.g. notice boards, village newsletters). At the information session, interested participants will provide researchers with their contact details and receive information sheets and consent forms. Those not interested in participating will be asked to complete a short questionnaire giving their age, sex and reasons why they declined participation. Residents who are interested in participating, but unable to attend the information session, will be provided with researchers’ contact details by village staff.

### Eligibility criteria

Eligible retirement villages will be those in the metropolitan area of Sydney, Australia, that: have at least 60 independent (self-care) residents; have a common facility area suitable for dance classes; and are not offering dance classes. A minimum of 12 participants from each retirement village will be recruited. Eligible participants in the trial must: be a resident of the village; agree to undergo physical and cognitive testing; and obtain medical clearance to participate in the study. Participants will be excluded if they: score less than 24 on the Mini Mental State Examination (MMSE) indicating cognitive impairment [30]; or plan to leave the village for three months or more during the trial.

### Screening for eligibility and baseline data collection

Researchers will contact interested participants in order to conduct a short telephone interview and to schedule a time for baseline measurement at the retirement village. During the baseline measurement session, researchers will first administer the MMSE to determine eligibility. Baseline measures will then be collected from eligible participants by up to three trained researchers. All participants will self-complete a questionnaire, and will undergo a series of physiological and psychological examinations as detailed below:

• The baseline questionnaire includes questions and scales addressing: demographics, physical activity [31], other leisure pursuits (e.g., reading, attending social clubs, games, cultural activity) [32] medical history, fall history, falls self-efficacy [33], quality of life assessments [34], depressive symptoms (15-item Geriatric Depression Scale (GDS)) [35], social networks [36], history of dancing and dance self-efficacy.

• Physiological measurements include the Physiological Performance Assessment (PPA) [37], the Short Physical Performance Battery (SPPB) [38], and Choice Stepping Reaction Time (CSRT) [39] with and without a cognitive load [40].

• Psychological measurements include the Trail Making Tests (TMT) part A and B [41] and the Rey Auditory Verbal Learning test (RAVLT) [42]. These tests are described in detail in the main outcomes section.

### Randomisation and allocation concealment

After completion of the baseline measures and obtaining all medical clearances, the study coordinator will provide the study statistician with village means of two baseline tests that predict falls and recurrent falls, the PPA [37] and TMT part B [5]. Retirement villages will be randomised to intervention or control group by the study statistician using a computer generated randomisation method, constrained using minimisation. That is, each village will be allocated with a probability of 0.8 to the group that minimises the imbalance of the means of these two baseline variables between intervention and control groups, using two strata for each variable. The statistician will advise the study coordinator of the village’s allocation and the study coordinator will arrange for delivery of the intervention if appropriate. Allocation will thus be concealed from the research team recruiting villages and participants, as randomisation will occur after baseline measures have been completed. Villages and participants will be considered to have entered the trial at the point of randomisation.

#### Intervention

Participants in the intervention villages will be offered 80 hours of dance classes during a 12-month period. Dance classes will run for one hour, twice a week for approximately 40 weeks (allowing for short breaks during the 12-month period). Intervention villages will be offered two major styles: 1) Folk dancing which will include a collection of dances from the US, UK, France, Italy, Israel and Greece; and 2) ballroom dancing which will include a collection of dances such as Rock and Roll, Foxtrot, Waltz, and Latin dances including Salsa and Rumba. Dance programs will not be manipulated to mimic exercise training as in aerobic dance classes, nor will they incorporate any specific strength or balance training as reported in a pilot RCT [17]. The aim is to test the efficacy of dance programs as offered in the community. However the intervention will be standardised across all sites via periodical workshops, a guidebook and a DVD developed by the dance coordinators. The dance classes will be taught at varying levels of complexity and the progression during the year will be gradual. Progression to new dances will take into account the balance challenge, cardiovascular demand, degree of flexibility, coordination and cognitive demand. Dance intensity will be monitored using accelerometers three times during the 12-month period (after 20, 40 and 60 hours of dance classes).

Retirement villages and participants in the control group will be advised to continue with their regular activities, and asked not to join a dance class during this time. Controls will be placed on a wait list for the dance classes.

All participants in the study will be sent monthly newsletters containing study updates, a “meet the team” section and a health education section (e.g., vitamin D, sleeping habits, healthy eating, smoking cessation, appropriate footwear, reducing alcohol intake, falls statistics and the origin of ballroom/folk dance). Further information contained in the monthly newsletters can be obtained by contacting the corresponding author.

### Primary and secondary outcomes and measures

The primary outcomes are:

1) Number of falls

2) Time to complete TMT parts A and B

The secondary outcomes are:

1) PPA score

2) CSRT with and without cognitive load

3) Lower limb functional status

4) Quality of Life

5) Cost per fall prevented

6) Cost per quality adjusted life year (QALY) gained

The details for each of these measures are given below.

*Number of falls during the 12 month trial*. A fall is defined as ‘unintentionally coming to rest on the ground, floor, or other lower level’ [43]. Participants are asked to record falls daily for the duration of the study using a monthly calendar (diary). Participants will be asked to record ‘F’ (Fall) or ‘N’ (no fall) each day on the calendar and return this by mail at the end of each month. Participants who report a fall will be interviewed by telephone to obtain specific details about where the fall occurred, resulting injuries and any treatment sought. Participants who fail to return their calendars within two weeks will be contacted by phone. They will inform the researchers over the phone of the entries in their calendar for the past month, and will also be asked also return their calendar by mail.

*Time to complete TMT Parts A and B*[41]. Part A measures processing speed and involves participants connecting consecutive numbers (e.g., 1-2-3). Part B is a measure of executive function of ‘task shifting’ and involves participants connecting alternating letters and numbers (e.g.,1-A-2-B). The difference in time between the two parts (B minus A) will be calculated to isolate the executive component of this test.

*The PPA* comprises five tests that provide a physiological fall risk score: vision (edge contrast sensitivity), peripheral sensation proprioception, lower extremity strength (knee extension), simple reaction time using a figure press as the response, and balance measured by body sway when standing on a medium-density foam rubber mat.

*CSRT with and without cognitive load*[39,40]. Two tests require the participant to perform quick, correctly targeted steps measured in milliseconds using a dance mat. In its simple form (test 1), participants see a graphical presentation of the four arrows on the mat (front left, front right, side left, side right) on a computer screen. The step direction is indicated by one arrow changing its colour. Participants are asked to step as quickly as possible onto the corresponding arrow of the mat and return to the centre (stance panels). The test consists of 4 practice trials (one trial for each step direction: side left, front left, front right, side right) and 32 test trials with stimuli occurring randomly between 1 and 2 seconds after the participant returns to the centre.

The second test (the Stroop stepping test) measures response inhibition and selective attention. For this test eight panels on the dance mat are used: 2 central stance panels, 2 front panels, 1 left panel, 1 right panel and 2 back panels. In the centre of the computer screen an arrow is presented pointing in one of four directions (up, down, left, right) that match the four possible step directions (forward, backward, left, right). Inside the arrow is a written word indicating a direction different to that indicated by the arrow. Participants have to step according to the word (ignoring the direction of the arrow) and then return to the centre panels. After 4 practice trials with one step in each direction, a random sequence of 20 trials in which the directions of word and shape never match commences. Participants step with the left foot to the left panel, with the right foot to the right panel and with either foot to the front and back panels. If participants step on a wrong panel they have to repeat the trial until they step correctly. In each of the three tests, reaction time measured from stimulus occurrence to movement initiation (lift off); movement time measured from movement initiation to step finalisation (step down) and stepping errors are measured.

*Functional mobility* will be assessed with the SPPB which includes tests of side-by-side, semi-tandem, and tandem standing, walking speed over 3 metres, and time to complete five chair rises.

*Quality of life* will be measured with the SF-12 _V_2 [44] and ICECAP-O [45] instruments at 3 and 12 months

### Mid-term and follow-up assessments

Physical activity and other leisure time activities will be measured at 6 months via telephone interviews. This is to monitor changes among participants in activities that can enhance performance on tests, apart from dancing. The self-completed quality of life questionnaire will be mailed to participants after 3 months from randomisation. All baseline measurements will be repeated at 12-month follow-up. Researchers performing all measurements will be blinded to group allocation and participants will be asked not to reveal to researchers which group their village was in.

#### Statistical analysis

Intention-to-treat analysis will be conducted. We will use negative binomial regression with a random effect with robust standard errors (to allow for clustering) [50] to estimate the magnitude of the intervention effect on number of falls. Generalised linear models with a random effect with robust standard errors will be used to estimate the intervention effect on cognitive measures [51]. The product-of-coefficient test and bootstrap methods will be used to estimate the mediating effects of physiological and cognitive measures of the intervention effect on falls [52]. All models will be fitted both unadjusted (primary analysis) and adjusted for PPA and TMT-B (the minimisation variables), age and sex, education, country of birth, main occupation, use of medications, chronic conditions, falls history and for baseline values for secondary outcomes other than cost. Both unadjusted and adjusted analyses will be reported. All statistical analysis will be blind to group identification. Sensitivity analysis will be used to assess the differential effects (if any) of different strategies of handling missing data (i.e. last observation carried forward, single imputation, multiple imputation) [53].

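### Mediation of the falls effect is to be estimated from measures repeated only at 12 months, so an effect of falls on those measures cannot be told apart from mediation

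*Protocol article*

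**What the plan says.** **The analysis.** The Statistical analysis section names the product-of-coefficients test and bootstrap methods, which "will be used to estimate the mediating effects of physiological and cognitive measures of the intervention effect on falls". It attaches no exploratory label and no remark on timing.

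**The candidate mediators.** The section on screening and baseline data collection lists the physiological battery (PPA, SPPB, CSRT) and the cognitive battery (TMT parts A and B, RAVLT).

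**When they are measured again.** Under Mid-term and follow-up assessments: "All baseline measurements will be repeated at 12-month follow-up". Two earlier contacts are described, and neither includes these tests: "Physical activity and other leisure time activities will be measured at 6 months via telephone interviews", and "The self-completed quality of life questionnaire will be mailed to participants after 3 months from randomisation".

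**When the falls are counted.** Under Primary and secondary outcomes and measures, the outcome is "Number of falls during the 12 month trial", and "Participants are asked to record falls daily for the duration of the study". No fall count after the 12-month tests is described.

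**The concern.** A product-of-coefficients analysis multiplies two paths: allocation to mediator, and mediator to outcome given allocation. To read the product as mediation, the mediator has to act before the outcome. Here the only post-randomisation value of each mediator is taken when the fall count is closing. Any association between 12-month performance and falls may run from performance to falls, from falls to performance, or both ways.

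The reverse direction is plausible from the document alone. The Background says that falls, even without injury, may bring fear, loss of independence and nursing home admission, and the economic section expects some hip fractures. Such events could lower knee strength, chair-rise time, sway or stepping speed, which are among the proposed mediators.

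At stake is an explanatory statement, for example that dance prevents falls by improving balance or executive function, made from data that cannot establish it.

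**Working it through.** **1. The plan's own figures, to confirm the inputs.** From the Sample size section: control rate 0.85 per person-year, rate ratio 0.63 (dance rate 0.85 × 0.63 = 0.5355), dispersion 0.79, two-sided 5%, 80% power.

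- n = (1.960 + 0.842)² × (1/0.85 + 1/0.5355 + 2 × 0.79) / (ln 0.63)² = 170.0, rounded up to **171**.
- Design effect 1 + 21 × 0.015 = 1.315; 171 × 1.315 = 224.9, giving **225**.
- 225 / 0.9 = **250**.

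All three match the article. With the 70% completion assumed for the cognitive tests, 250 × 0.70 = 175 per arm would have follow-up mediator values.

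**2. Timeline.**

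| Month | Falls | PPA, CSRT, SPPB, TMT, RAVLT | Other |
|---|---|---|---|
| 0 | counting starts | measured | – |
| 3 | counted daily | – | quality of life |
| 6 | counted daily | – | physical and leisure activity |
| 12 | counting ends | measured | – |

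No mediator value lies between randomisation and the end of the count.

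**3. Spurious share when true mediation is nil.** Assumptions that are not in the document: each fall worsens the 12-month mediator by g SD; dance improves the mediator directly by d SD; the correlation between baseline and 12-month values is ρ. For d, 0.35 is the article's planning effect for TMT-B and 0.25 is an assumed smaller value.

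- Path a (arm to mediator): −(d + g × (0.85 − 0.5355)).
- Path b (mediator to log fall rate, given arm and baseline), to first order: g × Σμ / Σ[μ/(1 + 0.79μ)] / V. Here Σμ = 0.85 + 0.5355 = 1.3855 and Σ[μ/(1 + 0.79μ)] = 0.5085 + 0.3763 = 0.8848, so b ≈ 1.566 g / V.
- V = (1 − ρ²) + g² × 1.091. The 1.091 is the mean of the two fall variances, 1.421 and 0.762, from μ + 0.79μ².
- Share = ab / ln 0.63, with ln 0.63 = −0.462.

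At g = 0.10, d = 0.35, ρ = 0.5: V = 0.761, b = 0.206, a = −0.381, ab = −0.0785, share = **17%**. The simulation of this setting gave an average ab of −0.078 and a share of 17%. At d = 0.25, ρ = 0.5 the formula gives about 13%, and at d = 0.35, ρ = 0.7 about 25%. At g = 0, b = 0 and the share is nil. The baseline mediator is already in both models, so adjusting for it does not remove the term in g.

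**4. How often mediation is falsely declared.** Simulated trials with negative binomial falls at the plan's values, 175–225 per arm, ρ 0.5–0.7 and clustering ignored. A linear model was used for the mediator and a negative binomial model for falls.

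| Worsening per fall (assumed) | Dance shifts mediator by 0.25–0.35 SD |
|---|---|
| 0 SD | about 0.5–5% |
| 0.05 SD | about 7–27% |
| 0.10 SD | about 26–80% (share 13–25%) |
| 0.15 SD | about 59–98% |

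If dance does not shift the mediator directly, the figure is about 6% or fewer over this range of g.

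These ranges correspond to a normal-theory (Sobel) test of the product. Simulated limits for the product, which are closer to a bootstrap, run somewhat higher: 48–84% at 0.10 SD with a shift, and 7.5% at 0.10 SD without one (d = 0, ρ = 0.5, 225 per arm). With a few hundred trials per setting, figures near 50% carry a standard error of about 2.5 points (√(0.25/400)).

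**The case against.** The strongest reply has four parts.

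- **The bias is conditional.** It needs falls to worsen the 12-month tests, and the document gives no figure for that. Several candidates (TMT, contrast sensitivity, proprioception, simple reaction time) have no stated route by which an ordinary fall would change them. This stands. A reader might infer that reverse causation will appear as mediation. The document supports only that it can appear and could not be recognised.
- **The size is driven by assumptions.** This also stands. One high percentage would mislead, because the result runs from nominal or below to near certainty across plausible inputs. The range has to be shown, including the small error when dance does not shift the mediator.
- **The analysis is supplementary.** Mediation takes one sentence, is not a listed primary or secondary outcome, and neither aim depends on it. A reader might infer that the link between the falls aim and the cognition aim is undermined. It is not: each aim has its own randomised comparison.
- **Details belong to the full analysis plan.** This holds for model form, covariates and interpretive limits. It does not cure the timing, because no analysis plan can supply mediator values or later falls that the described schedule does not collect.

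**Conclusion.** The point holds as a limit on what the mediation analysis can show. The schedule and the analysis are both stated outright, and together they leave temporal order unidentified. With nil true mediation and a direct effect of dance on the mediator, an assumed loss of 0.10 SD per fall gives a spurious share of 13–25% and a false declaration in roughly a quarter to four fifths of trials. At 0.05 SD the excess is modest, and at 0 SD there is none. These figures rest on the assumed per-fall loss, the assumed correlation and mediator shift, and the neglect of clustering. The timing argument does not rest on them.

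It would go too far to conclude that the trial's mediation result will be false, or that the analysis must be withdrawn. An association reported as such remains legitimate. The primary falls and TMT comparisons are not touched.

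**What to change.** In the Statistical analysis section, or in the analysis plan before unblinded analysis:

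- Restate the analysis as an exploratory association between change in the physiological and cognitive measures and falls over the same 12 months.
- State that temporal order cannot be established, because the measures are repeated only at 12 months.
- Report no causal indirect effect and no mediated proportion.
- Base any mechanistic statement on the randomised effects on PPA, CSRT, SPPB and TMT, which the plan already treats as outcomes.

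The cost is a change of wording and the loss of a causal mediation claim. No new data are needed, so the change remains possible although 12 villages are already randomised. Keeping a mediation claim would require interim mediator measurements related only to later falls, which is a change to data collection and far more expensive.

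### The primary analysis is unadjusted although villages are minimised on PPA and TMT-B and TMT has a baseline: valid, but inefficient, and even the adjusted model omits baseline TMT-A

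*Protocol article*

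**What the plan says.** **Allocation.** Under Randomisation and allocation concealment, the statistician receives the village means of PPA and TMT part B, and "each village will be allocated with a probability of 0.8 to the group that minimises the imbalance of the means" of these two variables, with two strata for each.

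**Outcomes.** Under Primary and secondary outcomes and measures, the second primary outcome is "Time to complete TMT parts A and B". The difference B minus A is also to be calculated. TMT is in the baseline battery, and Mid-term and follow-up assessments says "All baseline measurements will be repeated at 12-month follow-up".

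**Analysis.** Statistical analysis fixes the order of the models: "All models will be fitted both unadjusted (primary analysis) and adjusted for PPA and TMT-B (the minimisation variables". The adjusted model goes on to demographic and health covariates and ends with "falls history and for baseline values for secondary outcomes other than cost". It then commits that "Both unadjusted and adjusted analyses will be reported".

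**Sample size.** The TMT-B calculation uses d = 0.35, 80% power, the same design effect as for falls and 70% completion. It contains no baseline correlation, so it is a calculation for an unadjusted comparison.

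**The concern.** Two features of the design are not used in the analysis that decides the trial.

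- Villages are balanced on PPA and TMT-B because these are held to be prognostic. Balancing prognostic variables makes the between-group difference truly less variable. A model without those variables still counts their variation as noise, so taken by itself this makes the standard error too large and the test conservative.
- Individual baseline TMT is collected before randomisation and is normally one of the best predictors of the same test a year later. Leaving it out of the primary model gives up precision on a primary outcome.

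A third, smaller point concerns the adjusted model. Its own-baseline clause is worded "for baseline values for secondary outcomes other than cost". TMT-B enters by another route, as a minimisation variable. TMT-A belongs to a primary outcome and enters by neither route, so B minus A is adjusted for only one of its two baseline components. The text also does not say whether the TMT-B covariate is the individual value or the village mean used in minimisation.

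What is at stake is power and the width of confidence intervals, not bias.

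**Working it through.** **Inputs** (Sample size section unless noted): ICC 0.015; mean 22 per village; d = 0.35 for TMT-B; 80% power; 70% completing cognitive follow-up; 250 per group planned. The two-sided 5% level is stated for falls and taken to hold for TMT. The abstract gives about 450 participants, or about 225 per group. The correlation ρ between baseline and 12-month TMT is not in the document, so a range of 0.3 to 0.7 is assumed.

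**Step 1: the plan's own TMT figure.**
- Design effect = 1 + (22 − 1) × 0.015 = 1.315.
- Individually randomised n per group = 2 × ((1.960 + 0.842)/0.35)² ≈ 128.2, rounded up to 129.
- 129 × 1.315 = 169.6; divided by 0.70 = 242.3, so 243 per group.

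The protocol states 217, which these inputs do not reproduce. That is a separate matter. Here it is enough that the planned 250 covers 243 and that 225 does not.

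**Step 2: unadjusted power.** Effective n per group = N × 0.70/1.315. Power = Φ(0.35 × √(effective n/2) − 1.960).
- N = 250: effective n = 133.1; 0.35 × √66.5 = 2.855; Φ(0.895) = 81.5%.
- N = 225: effective n = 119.8; 0.35 × √59.9 = 2.708; Φ(0.748) = 77.3%.

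**Step 3: baseline-adjusted power.** Adjustment multiplies the outcome variance by (1 − ρ²), so d is divided by √(1 − ρ²). The design effect is held at 1.315. Example at N = 250, ρ = 0.5: 2.855/0.866 = 3.297; Φ(1.337) = 90.9%.

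| Assumed ρ | Power, 250 per group | Power, 225 per group | Recruited per group for 80% power |
|---|---|---|---|
| unadjusted | 81.5% | 77.3% | 243 |
| 0.3 | 84.9% | 81.0% | 220 |
| 0.5 | 90.9% | 87.9% | 183 |
| 0.6 | 94.6% | 92.3% | 156 |
| 0.7 | 97.9% | 96.7% | 124 |

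At 250 per group the gain is 84.9 − 81.5 = 3.4 points at ρ = 0.3 and 97.9 − 81.5 = 16.4 points at ρ = 0.7. In sample size the saving is (243 − 220)/243 = 9% to (243 − 124)/243 = 49%.

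**Step 4: if the response were change from baseline.** The article does not say whether the cognitive response is the 12-month value or the change. For change, the variance factor is 2(1 − ρ): 1.40, 1.00, 0.80 and 0.60 at ρ = 0.3, 0.5, 0.6 and 0.7. The adjusted model's factor (1 − ρ²) is 0.91, 0.75, 0.64 and 0.51. Adjustment is better at every value, although at the higher correlations the gap is smaller than in the table.

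**Step 5: which baselines the adjusted model holds.**

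| Primary measure | Own baseline in the adjusted model? |
|---|---|
| Falls | Yes, as falls history |
| TMT-B | Yes, as a minimisation variable |
| TMT-A | No |
| B minus A | Only the B part |

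**The case against.** The strongest reply is that nothing here is invalid. The primary model is named in advance, does not depend on a choice of covariates, and matches a sample size computed without adjustment. At 250 per group it has about 81% power, which meets the 80% target. The adjusted model is also pre-specified and will be reported, so readers will see any divergence. The gain depends on a correlation that the document does not give, and at 0.3 it is only about 3 points. All of this stands. It makes the point one of efficiency. It does not remove it, because the data are collected in any case and any non-zero correlation helps.

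A reader might infer more than the document supports:

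- *That baseline adjustment is confined to secondary outcomes.* It is not: TMT-B and falls history are in the adjusted model. Only TMT-A, and with it part of B minus A, is left out.
- *That deleting the word restricting the clause to secondary outcomes would cure the problem.* It would not, because the primary analysis lacks the baseline through being unadjusted.
- *That TMT will be a complete-case comparison, especially exposed to selective dropout.* The text never says complete-case. It specifies intention-to-treat and plans sensitivity analyses with several imputation strategies.
- *That falls loses a known amount of power.* The protocol describes PPA and TMT-B as predictors of falls but gives no strength of association, so no gain can be calculated.
- *That chance imbalance in PPA and TMT-B is a large hazard.* Minimisation limits exactly that imbalance.

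**Conclusion.** The point holds as one of efficiency. The primary analysis omits the minimisation variables and the TMT baseline. It is valid, but less precise than a model using data already in hand, and its standard errors tend to be conservative.

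For TMT-B at 250 per group, the cost is about 3 to 16 points of power for an assumed correlation of 0.3 to 0.7. At about 225 per group, the unadjusted comparison falls below target at 77%, while adjustment restores it to between 81% and 97%. These figures rest on the protocol's effect size, ICC and follow-up, a 12-month value as the response, an unchanged design effect after adjustment, and the assumed correlations. The conservatism is given as a direction only.

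The omission of baseline TMT-A from the adjusted model is a wording gap that stands without any of these assumptions.

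**What to change.** In Statistical analysis:

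1. Make primary a short pre-specified model: individual baseline PPA and TMT-B for all outcomes, plus each TMT measure's own baseline (including TMT-A, and both parts for B minus A) and, for falls, falls history.
2. Report the unadjusted model as supportive.
3. Keep the long covariate list (education, country of birth, occupation, medications and so on) as a sensitivity model.
4. Extend the own-baseline clause to primary outcomes, and state that the TMT-B and PPA covariates are individual values.
5. State whether the TMT response is the 12-month value or the change.

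The cost is wording only, since every covariate is already collected and an adjusted model is already planned. As 12 villages have been randomised, the change should be dated and made before anyone sees outcomes by group. Once both results are visible, switching the primary model would not be credible.
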